## Secondary objectives

1. To investigate the safety and tolerability of celgosivir

Hypothesis: The proportion of patients experiencing adverse events (AEs) or serious adverse events (SAEs) will be the same or lower in patients taking celgosivir than those taking placebo.

1. To investigate the effect of celgosivir on the time to viral clearance of dengue fever patients

Hypothesis: The time of viral clearance will be shorter for patients taking celgosivir than for those taking placebo

1. To investigate the effect of celgosivir on the serum NS1 of dengue fever patients

Hypotheses:

1. The mean serum NS1 concentration between Day 2 and Day 5 inclusive will be lower for patients taking celgosivir than for those taking placebo after adjusting for primary and secondary infection
2. The time to NS1 clearance will be shorter for patients taking celgosivir than for those taking placebo
3. To investigate the effect of celgosivir on the change in leukocyte and platelet counts of dengue fever patients

Hypothesis: The maximal change from baseline in leukocyte and platelet counts from Day 2 to Day 5 will be lower in patients taking celgosivir than those taking placebo

1. To investigate the effect of celgosivir on hemoconcentration in dengue fever patients

Hypothesis: The mean maximal hemoconcentration from Day 2 to Day 5 will be lower in patients taking celgosivir than those taking placebo

1. To characterize the population pharmacokinetics (PK) of celgosivir

Hypothesis: The clearance and volume of distribution of celgosivir will be dependent on weight and independent of age and sex.

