## Exploratory objectives

1. To investigate the effect of celgosivir on the immunological profile of dengue fever patients

Hypothesis: The maximal change from baseline between Day 2 and 5 will be lower for patients taking celgosivir than for those taking placebo for the following cytokines: (a) TNF- (b) IL-6, (c) IL-12, (d) interferon-, (e) IP-10 and (f) MCP-1.

1. To investigate the effect of celgosivir on the use of analgesic medications of dengue fever patients

Hypothesis: Patients taking celgosivir will use less analgesic medications from Day 1 to Day 5 than those taking placebo.

1. To investigate the effect of celgosivir on the intensity of joint and muscle pain of dengue fever patients

Hypothesis: Patients taking celgosivir will experience a lower intensity of joint and muscle pain from Day 2 to Day 5 than those taking placebo.

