Upon admission, a clinical examination will be conducted, including ECG and chest X-ray. Blood samples will be taken for baseline assessments - viremia, quantitative NS1, IgG specific for previous dengue infection, hematology and coagulation, clinical chemistry, immunological profile, pre-dose pharmacokinetics, and DNA and RNA analysis. Urine will be collected for a pregnancy test (female patients only) and urine protein/ creatinine ratio and urinalysis (all patients). The patient will be asked to complete a visual analog scale for pain (VASP). The patient will then be randomized to placebo or celgosivir group. Capsules will be administered without food from Day 1 to Day 5. Patients will be placed on a special diet of protein, vitamins, and glucose containing minimal complex sugars or starches. Oral fluid intake, urine output, and stool frequency and consistency will be recorded, as well as any adverse events. Daily clinical exams will be conducted. Blood samples will be drawn daily while in hospital for hematology and clinical chemistry, viremia, quantitative NS1 levels, and immunological profiling (RNA expression levels and cytokines). Any subject who has a platelet count drop of ≥50,000/mm3 over a 24 hour period will require full blood count monitoring every 12 hr henceforth until platelet count trend reverses. Urinalysis will be conducted daily, and a sample of urine will be reserved for PK drug levels. Patients also will be asked to complete a VASP daily. Pain medications and any other concomitant medications will be recorded (date/time of ingestion and amount). Over the course of the hospital stay, eight blood samples will be obtained for pharmacokinetic assessments: one pre-dose sample will be taken on Study Day 1, three samples will be obtained on Study Days 2 through 4 between 1 to 3 hr after ingestion of drug (peak levels), and four samples will be obtained on Study Days 2 through 5 immediately prior to ingestion of the next dose (trough levels). The date and time of pharmacokinetic blood draws will be recorded on the CRF. On Study Day 5, after blood draws, administration of the last dose, safety assessments, determination of risk for DHF or DSS, and satisfactory clinical status, the patient will be discharged. Patients at risk for or who have dengue hemorrhagic fever (DHF) or dengue shock syndrome (DSS) will be transferred to a medical ward of the hospital until fit for discharge. Patients who progress to DHF or DSS may require intravenous fluids, platelet and/or blood transfusions and evaluations from other clinical specialists. They will be treated according to standard of care for DHF and DSS--primarily bed rest, fluids, as well as fever and pain medications (supportive therapy).

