# Statistical Considerations

## Sample size calculation

To achieve 80% power to detect a difference of one log viremia reduction between the celgosivir treated group and the placebo group, assuming a standard deviation of one log, a sample size of 14 for each group (28 total) is required for a 5% one-sided type I error. With a sample size of 25 in each group (50 total), we are able to detect a difference of 0.7 log viremia reduction at a standard deviation of one log (equivalently a one log reduction at a standard deviation of 1.4 log) at 80% power.

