Viral clearance is indicated by an “undetectable” lab test results in the Dengue PCR at baseline, Day 2, Day 3, Day 4, Day 5 and Day 7. The time from baseline to viral clearance will be analyzed using a Kaplan-Meier analysis.

Serum NS 1 is measured by lab test results of “Dengue Non-structure protein 1”. The mean serum NS 1 between day 2 and Day 5 inclusive will be computed for each patient, and compared between the two groups using linear regression, adjusting for primary vs secondary infection. NS1 clearance is indicated by an undetectable lab test result in the NS1 assay. The time to NS1 clearance will be analyzed using a Kaplan-Meier analysis and compared using log rank test.

Leukocyte is measured by lab test results of “Urinalysis”, while platelet count is measure by the lab test results of “Hematology”. Both outcomes will be measured at baseline, Day 2, Day 3, Day 4 and Day 5. The maximum changes from baseline in leukocyte and platelet counts between Day 2 and Day 5 will be computed for each patient, and compared between the two groups using a two-sample t-test.

Hemoconcentration is defined as the hemaocrit at each day compared to that at Day 15. If the reference value at Day 15 is not available, use the value at Day 10. If both values at Day 10 and Day 15 are not available, the patient will be treated as a missing case. The mean maximal hemoconcentration from Day 2 to Day 5 will be computed for each patient, and compared between the two groups using a two-sample t-test.

Clearance celgosivir and volume of distribution of celgosivir will be obtained from concentration-time date by standard PK analysis. The correlation of these PK parameters with weight, age, and sex will be examined by nonlinear mixed effects modeling.

Exploratory outcomes

The various cytokines including TNF-, IL-6, IL-12, interferon-, and MCP-1, are measured by lab test results of “Cytokines” at Study Days 1, 2, 3, 4, 5, 7, 10, and 15. The maximal change from baseline (Day 1) in these cytokines between Day 2 and 15 will be computed for each patient, and compared between the two groups using two-sample t-test.

To investigate whether patients taking celgosivir will use less analgesic medications during the study, analgesic medications recorded during the in-hospital stay and the out-patient diary will between totaled. The total will be compared between the two groups using Fisher exact test.

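### The platelet and leukocyte endpoint is a maximum change from baseline with no stated direction; it should be defined as the largest decrease

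*Protocol*

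**What the plan says.** The protocol's Secondary objectives give the hypothesis: "The maximal change from baseline in leukocyte and platelet counts from Day 2 to Day 5 will be lower in patients taking celgosivir" than in those on placebo. The Statistical analysis section (Secondary outcomes) lists the measurement times, "Both outcomes will be measured at baseline, Day 2, Day 3, Day 4 and Day 5". It then fixes the per-patient statistic, "The maximum changes from baseline in leukocyte and platelet counts between Day 2 and Day 5 will be computed for each patient", and the test: the values are "compared between the two groups using a two-sample t-test". Whether this test is one- or two-sided is not stated, although the primary endpoints have one-sided tests.

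None of these sentences mentions a decrease, a nadir or an absolute value, and the protocol does not define the term elsewhere. The same paragraph takes leukocytes from urinalysis and platelets from haematology. Table 2 lists the white cell count and differential under haematology, drawn once before dosing and once on each of Days 2, 3, 4 and 5.

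**The concern.** The protocol fixes both the statistic and the direction that counts as success, so a definition that can be read three ways is more than a detail left for later. The readings are the signed maximum (the highest count minus baseline), the largest absolute change, and the largest fall.

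The context points to a fall. A "platelet count drop of ≥50,000/mm3 over a 24 hour period" triggers closer monitoring, and the exclusion criteria set lower limits for platelets and neutrophils. The endpoint itself does not say so. The Study Design summary counts leukocytes and platelets among the secondary endpoints for antiviral activity. If the reading is settled only when the data are analysed, the choice can change the sign or the strength of the result.

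**Working it through.** **The plan's own figure.** This endpoint has no power calculation. The only one in the protocol is for viremia: "a sample size of 14 for each group (28 total) is required for a 5% one-sided type I error", at 80% power for a difference of 1 log with SD 1 log. The noncentral t distribution gives 79.7% at 13 per group and 82.4% at 14, so 14 is right. Nothing below changes it.

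**Formulas.** Let B be the baseline count and C2 to C5 the counts on Days 2 to 5.
- Signed maximum = max(Cd − B)
- Largest absolute change = max|Cd − B|
- Largest fall = B − min(Cd)

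**Worked patients.** The counts are invented for illustration (platelets ×10³/mm³; leukocytes ×10³/µL).

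| Patient | B, then Days 2–5 | Signed maximum | Absolute | Fall |
|---|---|---|---|---|
| Deep platelet fall | 150; 120, 90, 60, 50 | 120 − 150 = −30 | 100 | 150 − 50 = 100 |
| Mild platelet fall | 150; 140, 130, 120, 115 | 140 − 150 = −10 | 35 | 150 − 115 = 35 |
| Steady platelet rise | 100; 105, 120, 140, 160 | 160 − 100 = +60 | 60 | 100 − 105 = −5 (no fall) |
| Leukocyte rebound | 4.0; 3.5, 3.0, 4.5, 6.5 | 6.5 − 4.0 = +2.5 | 2.5 | 4.0 − 3.0 = 1.0 |

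On the signed reading the deep fall has the lower value (−30 against −10), so the sicker patient looks better under a hypothesis that predicts lower values on drug. On the absolute reading the patient who never fell scores 60, worse than the mild fall at 35. The leukocyte rebound scores 2.5, worse than a patient who simply falls from 4.0 to 2.5 (1.5). Only the fall ranks all of them as the hypothesis intends.

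**Simulation.** There were 25 patients per arm (from the protocol), 4,000 trials per scenario and a one-sided 5% t-test. The protocol gives no count profiles, so these are assumptions. Each patient's changes are the arm's mean profile, plus a normal patient effect (SD 20, weighted 0.4, 0.7, 1 and 1.1 on Days 2 to 5), plus independent error (SD 15). Mean changes on Days 2 to 5, ×10³/mm³:
- S1, the drug halves the fall: placebo −20, −40, −55, −60; drug −10, −20, −28, −30.
- S2, smaller fall and recovery above baseline: placebo −20, −40, −45, −40; drug −10, −10, +15, +40.
- S3, milder disease with recovery to baseline: placebo −15, −25, −30, −30; drug −8, −12, −10, 0.

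Each cell gives the drug-minus-placebo difference and the share of trials significant in the hypothesised (lower) direction.

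| Scenario | Signed maximum | Absolute change | Largest fall |
|---|---|---|---|
| S1 | +14.7; 0% (opposite direction 93%) | −24.8; 99% | −26.6; 99% |
| S2 | +56.3; 0% (opposite 100%) | −7.7; 39% | −36.2; 100% |
| S3 | +16.7; 0% (opposite 92%) | −10.8; 72% | −17.8; 93% |

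**A second set of assumptions**, tested two-sided at 5%: baseline platelets about 160 (SD 35), mean fall 85 (SD 30), a 30% smaller fall on drug, measurement SD 8, nadir at 96 to 168 hours of illness, then recovery of 30 per day. The signed maximum was 8 units higher on drug with 45% power. The absolute change and the largest fall both had 82% power, and the fall was 21 units smaller on drug.

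**The case against.** The strongest reply is that a sensible analyst would not use the signed maximum, because it contradicts the stated hypothesis. A size-of-change reading fits that hypothesis best, and for platelets that stay below baseline through Day 5 it is the same number as the fall: 82% power for both under the second set of assumptions, 99% for both in S1. This stands, and it limits the practical damage. What remains is that the words chosen do not say so, and that the absolute reading fails when counts rebound past baseline.

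It can also be said that the protocol promises a detailed analysis plan before unblinding. That plan could settle the definition. But the protocol has already fixed the statistic and the direction of success, and a plan that follows it faithfully inherits the ambiguity.

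Third, the protocol never says outright that a leukocyte fall is the harm; its platelet trigger concerns platelets only. That is fair. The hypothesis treats the two counts alike and the neutrophil exclusion is a lower limit, so a decrease is the likely intent, but the sponsor should confirm it.

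A reader might also infer that outcome-dependent sampling biases the endpoint, since a patient with a steep platelet drop "will require full blood count monitoring every 12 hr henceforth until platelet count trend reverses". The documents do not support this. The Statistical analysis section lists only baseline and Days 2 to 5 as measurement times, and nothing says that the triggered counts enter the endpoint.

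**Conclusion.** The definition is ambiguous, and its literal reading reverses the hypothesis. The reversal follows from the formula: if the drug limits the fall, the highest post-dose count is also higher. It needs no assumed profile. The power figures do depend on the profiles. The absolute reading loses nothing while counts stay below baseline. Where counts on the drug recovered to or above baseline, it fell to 72% or 39%, against 93% or 100% for the largest fall.

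A reader might conclude that the planned analysis will lose most of the signal or report a benefit as a failure. That goes too far: it requires the signed reading, which fits the hypothesis least well. A reader might also extend the point to the cytokines, where the exploratory hypothesis is worded similarly ("The maximal change from baseline between Day 2 and 5 will be lower for patients taking celgosivir"). The wording is undirected there too, but the protocol names no direction of harm from which a largest rise could be prescribed.

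The consequence is limited to one secondary endpoint. The primary endpoints and the sample size are untouched.

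**What to change.** In the Secondary objectives and the Statistical analysis section, define the endpoint as the largest decrease: baseline minus the lowest of the scheduled Day 2, 3, 4 and 5 counts, with a smaller decrease favouring celgosivir. Say that a patient who never falls below baseline keeps the resulting negative value. State whether the test is one- or two-sided. Correct the leukocyte source to the haematology blood count in Table 2, and confirm that a decrease is the intended direction for leukocytes as well as platelets.

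Keep every scheduled count in the main intention-to-treat comparison. Removing counts taken after a platelet transfusion would delete post-randomisation data in the sickest patients, so any such exclusion belongs in a sensitivity analysis only.

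The cost is a few words before unblinding, with no new samples, visits or patients. Any deeper nadir seen only in a triggered 12-hourly count is left out of the efficacy comparison; it can still be reported with the safety data.

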### Exclusion Criteria

1. Clinical signs and symptoms for severe dengue, such as:
   1. Severe abdominal pain
   2. Persistent vomiting
   3. Clinical fluid accumulation
   4. Mucosal bleed
   5. Altered mental state
   6. Liver enlargement > 2 cm
   7. Systolic blood pressure < 90 mm Hg
   8. Pulse pressure < 20 mm Hg
2. A person with any of the following laboratory values:
3. Hematocrit >52% males; >46% females
4. AST or ALT  1000 U/L
5. Room air oxygen saturation <95%
6. Absolute neutrophil count <1500 /µL
7. Platelet count <80,000/mm3
8. Creatinine >165 µmol/L males; > 130µmol/L females
9. Hemoglobin <13.0 g/dL males; <11.0 g/dL females
10. Total Bilirubin > 24 µmol/L
11. Serum creatine kinase > 600 U/L
12. History of or presently active intestinal disorders such as peptic ulcers, intestinal ulcers, intestinal obstructions, intestinal hernias, ulcerative colitis, malabsorption syndrome, celiac disease, Roemheld’s syndrome (gastroesophageal regurgitation disease) or Crohn’s disease
13. Severe diarrhea (grade 2 or higher according to NIH clinical trials guidelines)
14. Current usage of any anticoagulant drugs including, but not limited to, aspirin, warfarin, or clopidogrel
15. Any other clinically significant acute illness within 7 days prior to first study drug administration.
16. History of severe drug and/or food allergies.
17. Exposure to any new investigational agent within 30 days prior to the study drug administration.
18. Clinically significant abnormal physical examination unrelated to dengue infection, chest X-ray or 12-lead electrocardiogram (ECG) at screening, such as QTc prolongation (>450 msec).
19. Females of childbearing potential who are pregnant, breast feeding, or unwilling to avoid pregnancy by the use of appropriate contraception, including oral and subcutaneous implantable hormonal contraceptives, condoms, diaphragm, or intrauterine device (IUD), during the period that the experimental drug is administered. Prospective female participants of childbearing potential must have a negative pregnancy test (point of care)

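### The platelet, leukocyte and cytokine changes are compared by t-tests that ignore the baseline value already collected; the tests are valid but usually give up precision (minor, free improvement)

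*Protocol*

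**What the plan says.** Section 6.2 of the protocol, Secondary outcomes, defines one value per patient for each blood count: "The maximum changes from baseline in leukocyte and platelet counts between Day 2 and Day 5 will be computed for each patient". The arms are then "compared between the two groups using a two-sample t-test". The preceding sentence confirms that the baseline is there to be used: "Both outcomes will be measured at baseline, Day 2, Day 3, Day 4 and Day 5".

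Under Exploratory outcomes in the same section the cytokines are handled alike: "The maximal change from baseline (Day 1) in these cytokines between Day 2 and 15 will be computed for each patient", and the result is "compared between the two groups using two-sample t-test".

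Section 5.1 places the baseline sampling at admission, ahead of randomization: "Blood samples will be taken for baseline assessments - viremia, quantitative NS1, IgG specific for previous dengue infection, hematology and coagulation". That list goes on to include the immunological profile, so the Day 1 cytokines are covered as well.

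Covariate adjustment is used once in 6.2. Mean serum NS1 is "compared between the two groups using linear regression, adjusting for primary vs secondary infection". No such term is named for the counts or the cytokines. Section 6.2 also says that a detailed analysis plan will be written before unblinding.

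**The concern.** A t-test on change from baseline fixes the slope of follow-up on baseline at exactly 1. If the true slope differs from 1, part of the baseline variation stays in the change score as noise, and a chance difference in entry values between the arms carries into the treatment contrast. A linear model with the baseline value as covariate estimates the slope instead.

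Section 3.1 names leukocyte and platelet counts among the secondary endpoints for antiviral activity. With 25 patients per arm precision is scarce, and chance imbalance at entry can be sizeable. Randomization uses permuted blocks (5.2), and no stratification by entry counts is described. What is at stake is the precision of these secondary and exploratory comparisons, not the validity of the test and not the primary analyses.

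**Working it through.** **The protocol's own figures.** Section 6.1 powers only the viremia endpoint: 14 per group for a 1 log difference with SD 1 log, one-sided 5%, 80% power. The exact t calculation gives 13.1, rounded up to 14 (power 82.4% at 14). With 25 per group, power for 0.7 log at SD 1 is 78.7% by the t distribution and 79.7% by the normal formula. These figures reproduce. No power figure exists for platelets, leukocytes or cytokines.

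**Inputs.**
- 25 per arm, 1:1 (3.1).
- 5% significance level (6.2). The sidedness of these particular tests is not stated; two-sided is assumed.
- Rho: not in the protocol; range 0.3 to 0.9 assumed.
- k, the follow-up SD divided by the baseline SD: not in the protocol; 0.8 to 1.43 assumed.
- Starting point: the effect for which the t-test on change has 80% power, which is 0.809 SDs of the change score. This is a reference point, not a claim in the protocol.

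**Variance ratio.** Let s be the baseline SD.
- Change score: s²(1 + k² − 2·rho·k).
- Adjusted model, residual: s²·k²(1 − rho²).
- Ratio: k²(1 − rho²)/(1 + k² − 2·rho·k). For k = 1 this is (1 + rho)/2.

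The adjusted variance is multiplied by 1 + 1/46 for estimating the slope. Power comes from the noncentral t with 47 df.

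**Equal SDs (k = 1).**

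| rho | variance ratio | adjusted power | patients the t-test needs to match 50 (50/ratio) |
|---|---|---|---|
| 0.3 | 0.65 | 93% | 77 |
| 0.5 | 0.75 | 89% | 67 |
| 0.7 | 0.85 | 85% | 59 |
| 0.9 | 0.95 | 81% | 53 |

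The last column leaves out the small slope-estimation cost. One-sided 5% testing gives nearly the same powers: 92%, 88%, 85% and 81%.

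**Unequal SDs.**

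| k | rho | slope (rho·k) | variance ratio | adjusted power |
|---|---|---|---|---|
| 1.2 | 0.3 | 0.36 | 0.76 | 89% |
| 1.2 | 0.5 | 0.60 | 0.87 | 84% |
| 1.2 | 0.7 | 0.84 | 0.97 | 80.5% |
| 1.2 | 0.8 | 0.96 | 1.00 | 79% |
| 1.2 | 0.9 | 1.08 | 0.98 | 80% |
| 1.43 | 0.7 | 1.00 | 1.00 | 79% |
| 0.8 | 0.7 | 0.56 | 0.63 | 94% |

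The gain is larger when the follow-up SD is the smaller one. It disappears, and turns into a loss of about 1 point, where the slope is close to 1.

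**Does taking an extreme value change this?** The planned endpoint is the largest of four changes, so the lowest of four post-baseline values minus baseline was simulated (25 per arm, 4,000 runs per setting, equal SDs and a common correlation between days). Variance ratios were about 0.55, 0.69, 0.83 and 0.95 at rho 0.3, 0.5, 0.7 and 0.9. Power for t-test against adjusted model was 84% against 97%, 84% against 94%, 84% against 89%, and 83% against 84%. With no effect, both methods rejected in 4.4% to 5.4% of runs, and both estimates centred on zero.

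**Chance imbalance.** The SD of the baseline mean difference is √(2/25) = 0.283 baseline SDs, with 95% limits ±1.96 × 0.283 = ±0.55. With equal SDs, an imbalance of 0.55 moves the change-score contrast by (1 − rho) × 0.55 in the opposite direction: 0.39, 0.28 and 0.17 SDs at rho 0.3, 0.5 and 0.7. The adjusted model removes this shift.

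**The case against.** The planned test is legitimate. Under randomization the t-test on change is unbiased and holds its error rate, as the null simulations show. The outcomes are secondary or exploratory, the sample size does not rest on them, and the analysis plan still to be written could add a covariate. All of this stands and keeps the point minor. It does not remove the point, because the protocol names the unadjusted test for these outcomes rather than leaving the choice open.

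Three stronger readings are tempting, and the documents support none of them.
- A reader might infer that regression to the mean biases the comparison. It acts on both arms alike. Only a chance baseline imbalance carries through, and that averages out over randomizations.
- A reader might infer that adjustment always wins, or always gains at least some fixed amount. Neither rho nor the SDs are given, and the unequal-SD table shows gains from large to slightly negative.
- A reader might take the criterion "Platelet count <80,000/mm3" as a floor that limits how far counts can fall. It is an exclusion at entry (3.2.2) and puts no limit on later counts.

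It is also fair to say that a covariate does not repair other problems in the same text. Section 6.2 takes leukocytes from the urinalysis results, whereas the assessment schedule (Table 2) lists the white-cell differential under hematology. The cytokine window runs to Day 15 in 6.2 but to Day 5 in the exploratory objectives (2.3).

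**Conclusion.** The point holds as a matter of efficiency. Section 6.2 fixes an unadjusted t-test on change for platelets, leukocytes and cytokines while the baseline value is in hand. Against 80% power for the t-test (25 per arm, two-sided 5%), the baseline-adjusted model has about 93% to 81% power over rho 0.3 to 0.9 with equal SDs. With a follow-up SD 1.2 times the baseline SD it ranges from about 89% down to 79%. The gain is material at low to moderate correlation, negligible near rho 0.9 with equal SDs, and about −1 point where the slope is near 1. These sizes rest on an assumed rho and SD ratio, and they apply to the cytokines only if the same assumptions suit them. Severity: minor; a free improvement. No primary conclusion is affected.

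**What to change.** In 6.2, before unblinding, replace these t-tests with a linear model of the same endpoint on treatment and the patient's own baseline value, and report the adjusted difference with its 95% CI. Do the same for the cytokines, with the Day 1 value as covariate and on the log scale if the values are skewed.

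Before the leukocyte baseline is used, reconcile its source between 6.2 and Table 2. Settle the cytokine window between 2.3 and 6.2 in the same edit.

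The cost is a wording change in 6.2, carried into the analysis plan, and one degree of freedom per model. No new data are needed. The change should be fixed before unblinding, because a covariate added afterwards could be challenged as chosen from the results.

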| Time (Hr) relative to first dose | -14 to 0 | | **0+/-1hr** | 0 to 3 | **11 to 12+/-1hr** | 23 to 24 | **24+/-1hr** | 24 to 27 | **35 to 36+/-1hr** | 47 to 48 | **48+/-1hr** | 48 to 51 | **59 to 60+/-1hr** | 71 to 72 | **72+/-1hr** | 72 to 75 | **83 to 84+/-1hr** | 95 to 96 | **96+/-1hr** | 96 to 99 | 144 ± 24 | 216 ± 24 | 336 ± 24 |
| **Evaluation & Administrative Assessments** |  | |  |  |  |  |  |  |  |  |  |  |  |  |  |  |  |  |  |  |  |  |  |
| Demographics | + | |  |  |  |  |  |  |  |  |  |  |  |  |  |  |  |  |  |  |  |  |  |
| Medical History | + | |  |  |  |  |  |  |  |  |  |  |  |  |  |  |  |  |  |  |  |  |  |
| Informed Consent | + | |  |  |  |  |  |  |  |  |  |  |  |  |  |  |  |  |  |  |  |  |  |
| NS1 Strip Assay - test kits provided by Duke | + | |  |  |  |  |  |  |  |  |  |  |  |  |  |  |  |  |  |  |  |  |  |
| Clinical Exam h | + | |  |  | ~~+~~ | ~~+~~ |  |  | ~~+~~ | ~~+~~ |  |  | ~~+~~ | ~~+~~ |  |  | ~~+~~ | ~~+~~ |  | ~~-~~ | ~~+~~ | ~~+~~ | ~~+~~ |
| Body Weight and Height a | + | |  |  | + | + |  |  | + | + |  |  | + | + |  |  | + | + |  |  | + | + | + |
| Vital Signs (Body Tb, BP c, PR c, O2 saturation c) | + | |  | + | + | + |  | + | + | + |  | + | + | + |  | + | + | + |  | + | + | + | + |
| Hematology (FBC and WBC differential) - EDTA tubeg | + | |  |  |  | + |  |  |  | + |  |  |  | + |  |  |  | + |  |  | + | + | + |
| PT/PTT | + | |  |  |  |  |  |  |  |  |  |  |  |  |  |  |  |  |  |  |  |  |  |
| Clinical chemistry (full renal and liver panel) - plain tube | + | |  |  |  | + |  |  |  | + |  |  |  | + |  |  |  | + |  |  | + | + | + |
| GXM (PRN)d |  | |  |  |  |  |  |  |  |  |  |  |  |  |  |  |  |  |  |  |  |  |  |
| ECG | + | |  | + |  |  |  | + |  |  |  | + |  |  |  | + |  |  |  | + | + |  | + |
| Chest X-ray | + | |  |  |  |  |  |  |  |  |  |  |  |  |  | + |  |  |  |  |  |  |  |
| Pregnancy Assay in Females (Urine) | + | |  |  |  |  |  |  |  |  |  |  |  |  |  |  |  |  |  |  |  |  |  |
| Urinalysis | + | |  |  |  | + |  |  |  | + |  |  |  | + |  |  |  | + |  |  | + |  |  |
| Urine protein/creatinine ratio | + | |  |  |  | + |  |  |  | + |  |  |  | + |  |  |  | + |  |  | + |  |  |
| Dengue IgM |  | |  |  |  |  |  |  |  |  |  |  |  |  |  |  |  |  |  |  | + |  |  |
| Dengue IgG | +  + | |  |  |  |  |  |  |  |  |  |  |  |  |  |  |  |  |  |  |  |  |  |
| Drug Administration (capsules) |  | | 4 |  | 2 |  | 2 |  | 2 |  | 2 |  | 2 |  | 2 |  | 2 |  | 2 |  |  |  |  |

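### The hemoconcentration t-test leaves the already collected pre-dose hematocrit unused: it is valid, but gives up precision that a baseline-adjusted regression could recover

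*Protocol*

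**What the plan says.** The objective (protocol section 2.2) is: "The mean maximal hemoconcentration from Day 2 to Day 5 will be lower in patients taking celgosivir than those taking placebo".

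Section 6.2, under secondary outcomes, fixes the analysis:
- Reference: "Hemoconcentration is defined as the hemaocrit at each day compared to that at Day 15".
- Fallback: "If the reference value at Day 15 is not available, use the value at Day 10".
- No late value: "If both values at Day 10 and Day 15 are not available, the patient will be treated as a missing case".
- Summary and comparison: "The mean maximal hemoconcentration from Day 2 to Day 5 will be computed for each patient, and compared between the two groups". The test named is the two-sample t-test, with no covariate.

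The pre-dose hematocrit exists for every patient. Section 5.1 lists the blood taken on admission, before randomization, as including "hematology and coagulation, clinical chemistry, immunological profile, pre-dose pharmacokinetics, and DNA and RNA analysis". The row "Hematology (FBC and WBC differential) - EDTA tubeg" of Table 2 is marked in the screening and baseline column, on Days 2 to 5, and on Days 7, 10 and 15. The exclusion criteria in section 3.2.2 also need the value, since they cap hematocrit by sex.

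By contrast, section 6.2 scores platelets and leukocytes as change from baseline, and compares mean NS1 by a regression adjusted for primary versus secondary infection.

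**The concern.** Patients may enter after up to 48 hours of fever with any hematocrit below the exclusion cap, so some hemoconcentration can be present before the first capsule. Section 5.2 describes permuted blocks and states no stratification. Hemoconcentration already present at entry is therefore counted in the Day 2 to Day 5 maximum, and a chance difference between arms at entry can carry into the comparison.

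In addition, every in-hospital value is set against one late reading, so any error in that reading enters the outcome in full. A pre-dose value set against the same reading carries the same error. Adjusting for it would remove part of both sources of noise. At stake is the precision of one secondary efficacy comparison with 25 patients per arm.

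**Working it through.** **1. The plan's own figures.** The only power calculation (section 6.1) concerns viremia: a 1 log difference, SD 1 log, one-sided 5%, 80% power. The noncentral t distribution gives 79.7% power at 13 per group and 82.4% at 14, so the stated 14 reproduces. At 25 per group and 0.7 SD, one-sided, it gives 78.7% (79.7% by normal approximation), which agrees with the stated 80%. Nothing is stated for hemoconcentration.

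**2. Mechanism.** Write
- Day t hematocrit = H + c0 + g_t + e_t
- pre-dose hematocrit = H + c0 + e_0
- Day 15 hematocrit = H + e_15

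Here H is the patient's own level, c0 the excess at entry, g_t the later change and e the reading error. Taking the comparison as a difference (a ratio behaves alike on the log scale):
- outcome = c0 + max(g_t + e_t) − e_15
- pre-dose hemoconcentration = c0 + e_0 − e_15

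Both contain c0 − e_15, so they are correlated when the entry excess persists or when the reference is noisy.

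**3. Power with adjustment.** Inputs: 25 per arm (section 3.1); 5% level (section 6.2). Assumed: two-sided, since the protocol states one-sided only for the primary tests; a true difference of 0.7 SD, borrowed from the viremia calculation; entry-outcome correlation r. Residual variance is multiplied by 1 − r². The noncentrality is 0.7 / (√(1 − r²) × √(2/25)), on 47 df (48 for the t-test).

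| Analysis | Residual variance | Power | Gain (points) |
|---|---|---|---|
| t-test | 1 | 67.9% | – |
| adjusted, r = 0.3 | 0.91 | 71.9% | 4.0 |
| adjusted, r = 0.5 | 0.75 | 79.9% | 12.0 |
| adjusted, r = 0.7 | 0.51 | 92.4% | 24.5 |

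The gain depends on the starting point. At 0.81 SD, where the two-sided t-test has 80% power, and with a small penalty for estimating the slope, adjusted power is 79% (r = 0), 83% (0.3), 89% (0.5) and 97% (0.7). One-sided at 0.7 SD, power goes from 79% to 82% at r = 0.3.

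**4. Simulation of the endpoint itself.** Assumed: entry SD 5 points, a true 4-point reduction, 25 per arm, two-sided 5%.

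| Day-to-day correlation | 2.5% reading error | 1% reading error |
|---|---|---|
| 0 | 84% to 84% | 96% to 96% |
| 0.3 | 79% to 82% | 93% to 94% |
| 0.6 | 74% to 83% | 88% to 92% |
| 0.8 | 70% to 87% | not run |

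Each cell shows t-test power, then adjusted power. With no true effect, both analyses reject close to 5% of the time.

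**5. Chance imbalance at entry.** With the assumed SD of 5 points, the true difference between arm means has SD 5 × √(2/25) = 1.41 points, a 95% range of ±1.96 × 1.41 = ±2.8. Only a fraction reaches the treatment estimate. The fitted slope ran from about 0.15 to 0.6 over the settings tried, so ±2.8 becomes 0.15 × 2.8 = ±0.4 to 0.6 × 2.8 = ±1.7 points.

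**6. Which covariate.** In a further simulation, raw pre-dose hematocrit as sole covariate changed power by only −1 to +3 points: H cancels from the outcome but dominates that covariate. Modelling the Day 2 to 5 maximum on pre-dose hematocrit without the late reference lost about 5 points when the entry excess had largely resolved. Pre-dose hemoconcentration against the same late reference gained in every setting.

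**The case against.** - *The endpoint is coherent and the test valid.* This stands. A convalescent reference is a sensible way to define hemoconcentration and already removes each patient's own level. A reader might infer from the unused baseline that the comparison is biased. It is not: randomization balances entry hemoconcentration in expectation, and simulated type I error is near 5%.
- *The contrast with platelets and leukocytes is weak.* Largely right. Those endpoints are defined as change from baseline, and they too are compared by plain t-tests.
- *Covariates belong in the SAP.* A detailed plan is promised before unblinding and could add one. But the protocol does not leave the test open for this endpoint; it names it: "compared between the two groups using a two-sample t-test".
- *The covariate contains a post-randomization value.* True, and it should be stated. The outcome already contains the same value, so no new assumption is added. With a 2% shift of the reference in one arm and no true effect on Days 2 to 5, the t-test rejected 27% of the time and the adjusted analysis 15%: adjustment lessens that problem without curing it.
- *The gain may be nil.* This stands at low correlation with small reading error, where adjustment can cost about 1 point of power.
- *Dilution from study blood draws.* A reader might suspect that these distort the Day 15 reference. The planned draws are the same in both arms, and the protocol gives nothing from which to size such an effect.

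**Conclusion.** The point holds as one of efficiency. Section 6.2 fixes an unadjusted comparison although a relevant pre-dose value is collected in every patient. The cost is precision and exposure to chance imbalance, not validity.

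The size rests on assumptions, because the protocol gives no hematocrit SD, correlation, reading error or effect. The range runs from no gain, through about 3 to 5 points of power at an entry-outcome correlation of 0.3, to 12 or more from 0.5 upward. That last figure applies to a 0.7 SD difference tested two-sided; starting from 80% power, the gain at 0.5 is 9 points.

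A reader might go on to infer that chance imbalance at entry is as large as the effect the trial seeks. The documents do not support this. The protocol states no hemoconcentration effect (the 4 points used above are an assumption), and only part of the imbalance reaches the estimate. This is an optional improvement to a secondary endpoint.

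**What to change.** In section 6.2, for this endpoint only, replace the two-sample t-test by a linear regression of each patient's maximal Day 2 to Day 5 hemoconcentration on treatment arm. Use pre-dose hemoconcentration as covariate: the pre-dose hematocrit against the same Day 15 or Day 10 reference, in the same form (difference or ratio) as the outcome. Report the adjusted difference with its 95% CI. Note that the covariate shares the outcome's post-randomization reference, and keep the unadjusted t-test as a sensitivity analysis. Raw pre-dose hematocrit as the sole covariate is not an adequate substitute.

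The cost is a sentence or two in section 6.2 or the SAP before unblinding, and one degree of freedom. No new samples or visits are needed, and no further patients become missing, since the pre-dose value is already required for eligibility.
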